## Abstract

**Background:**

Fibromyalgia (FM) is a prevalent and disabling disorder characterized by a history of widespread pain for at least three months. Pain is considered a complex experience in which affective and cognitive aspects are crucial for prognosis. The aim of this study is to assess the importance of pain-related psychological constructs on function and pain in patients with FM.

**Methods:**

**Discussion:**

In recent years, the relevance of cognitive and affective aspects for the treatment of chronic pain, not only in FM but also in other chronic pain diseases, has been widely acknowledged. However, the relative importance of these psychological constructs, the relationship and possible overlapping between them, or the exact meaning of them in pain are not enough known.

## Background

Fibromyalgia (FM) is a prevalent and disabling disorder characterized by a history of widespread pain for at least three months and patient reporting of tenderness in at least 11 out of 18 defined tender points when digitally palpated with about 4 kg per unit area of force [1]. In addition to pain, the patient suffers from other symptoms such as non-restorative sleep, paraesthesia, difficulties in concentration and memory, stiffness, depression and anxiety [2]. FM is a common disorder; its prevalence within the community has been established in the range of 2-3%, predominantly in women in their third to fifth decade [3]. The aetiology of FM is uncertain but the existence of central sensitization is widely accepted [4]. Many treatments have been used in these patients but their efficacy is rather limited [5]. Due to its high prevalence, severe disability, low quality of life for the patient and significant health costs, FM is considered a public health problem [6,7].

Pain is the most common and disabling symptom in FM. The neurobiology of the pain process in FM using neuroimage techniques has developed greatly in recent years, identifying what has been called "pain matrix", which includes the primary and secondary sensory-motor cortex, insula, anterior cingulate, thalamus, dorso-lateral prefrontal cortex and basal ganglia [8-10].

Pain is considered a subjective and complex experience, in which affective and cognitive aspects are crucial for prognosis. At present, classical approaches focusing on modifying coping strategies [11] or on the cognitive restructuring of pain [12] are being widened to include other treatments based on pain acceptation and other psychological constructs. Some of the most important of these constructs are the following:

- *Pain catastrophizing: *This is the most studied pain-related construct. It has been described as an exaggerated negative orientation towards pain stimuli. It is made up of three dimensions: a) rumination: incapacity to avoid thinking about pain; b) magnification: exaggeration of the impact that pain produces; and c) helplessness: the feeling that one cannot free without overcome pain [13]. Some of the consequences that have been associated with pain catastrophizing in patients with chronic pain are more intense pain, heightened pain behaviour, greater consumption of analgesics, reduced involvement in daily activities, occupational disability and suicidal ideation [13,14].

- *Pain Acceptance *[15,16]: This is one of the most promising and valuable pain-related constructs. It comes from contextual or third wave psychotherapies and involves the individual reducing unsuccessful attempts to avoid or control pain and focusing instead on participation in valued activities and the pursuit of personally relevant goals. Some studies have demonstrated that patients with chronic pain and high pain acceptance present less pain, anxiety and depression, and better occupational status. Acceptation is associated with better adaptation to pain independently of pain severity, anxiety or depression.

- *Mental defeat *[17]: This is a recently described cognitive phenomenon not previously assessed in chronic pain, but thoroughly studied in other disorders such as depression and post-traumatic stress disorder. It can be defined as the perceived loss of autonomy in the face of uncontrollable traumatic events, resulting in the person giving up efforts to retain identity and self-will. With regard to pain, mental defeat can be considered a type of self-processing in which repeated episodes of persistent and disabling pain generate negative thoughts on pain and oneself.

- *Pain psychological inflexibility *[18]: From the point of view of third-generation psychotherapies such as acceptation and commitment therapy (ACT), observing external phenomena separately from our thoughts is crucial if we are to act in accordance with our aims and values. The inability to maintain our values in the presence of painful or disabling physical symptoms, emotions and thoughts has been called psychological inflexibility.

- *Perceived injustice *[19]: In situations in which the injury or disease has been produced as a result of negligence or a mistake caused by others (at least from the patient's point of view), the victim experiences his life with a feeling of injustice. The key point in this regard is the feeling of unnecessary suffering that can be blamed on another, requiring reparation from society. There is a clinical perception, which has not been systematically studied, that a feeling of perceived injustice is associated with poor recovery in chronic pain disorders [19].

- *Mindfulness: *This concept is defined as the practice of being mindful, focused on the present moment and without judging the situation we have to live through [20]. It has been demonstrated that mindfulness correlates positively with several measures of psychological well-being and that it is associated with significant long-term improvement in patients with pain and, specifically, in FM [20,21].

- *Positive and negative affect: *Affect has been described as the observable expression of emotion, which can be both positive and negative [22,23]. Negative affect has been related with poor outcomes in FM [22,23], but recently the emphasis has been put on the affect balance style (relative levels of negative and positive affect) as a prognostic marker in FM [24].

It is not currently known whether these psychological constructs correlate between themselves or even overlap each other. In addition, their specific significance for prognosis and treatment on chronic pain disorders has not been assessed. The general aim of this study is to assess the importance of pain-related psychological constructs on function and pain in patients with FM. The specific objective is to assess correlations and possible overlapping among constructs.

## Methods/Design

### Design

Multicentric, naturalistic, one-year follow-up study.

### Setting and study sample

Patients will be recruited from any of the primary care health centres in the region of Aragon, Spain. General practitioners will include patients with FM fulfilling the study criteria until the required sample is completed, without a quota of patients assigned for each centre.

Patients considered for inclusion are those aged 18-65 years, able to understand and read Spanish, who fulfil criteria for primary FM according to the American College of Rheumatology [1], with no previous psychological treatment, and on providing signed informed consent. Those excluded will be patients with severe Axis I psychiatric disorders (dementia, schizophrenia, paranoid disorder, alcohol and/or drug use disorders), severe Axis II disorders or somatic disorders which, from the clinician's point of view, prevent patients from carrying out a psychological assessment.

### Measurements

The variables and instruments of measurement are summarized in Table 1.

**Table 1 T1:** Study variables

Instrument	Assessment area	Time(s) of assessments	Applied by
Sociodemographic data form assistant	Sex, age, marital status, educational level, occupation, income	Baseline	Research

Clinical variables	Family & personal medical & psychiatric history, length of the disorder, main symptoms, psychiatric comorbidity	Baseline	Research

SPPI psychiatric interview [37]	Psychiatric diagnosis	Baseline	Psychiatrist
Pain catastrophizing scale [31]	Severity of catastrophizing	Baseline	Research

Pain acceptance scale [32]	Acceptation of pain	Baseline	Research

Pain Self-Perception Scale (PSPS) [33]	Mental defeat	Baseline	Research

Psychological Inflexibility in Pain Scale (PIPS) [34]	Pain psychological inflexibility	Baseline	Research

Injustice Experience Questionnaire (IEQ) [19]	Perceived injustice	Baseline	Research

Mindful Attention Awareness Scale (MAAS) [21]	Mindfulness	Baseline	Research

Positive & Negative Affect (PANAS) [36]	Positive and Negative Affect	Baseline	Research

Hospital Anxiety Depression Scale (HADS) [40]	Anxiety, depression	Baseline	Research

Fibromyalgia Impact Questionnaire [26]	General function	Baseline and follow-up	Research

Pain Visual Analogue Scale (PVAS) [29]	Pain	Baseline and follow-up	Research

Pain assessed by sphygmomanometer [30]	Pain	Baseline and follow-up	Research

#### Main outcome variables

- Fibromyalgia Impact Questionnaire (FIQ) [25]: The FIQ is a 10-item self-report questionnaire developed to measure the health status of FM patients. The first item focuses on the patient's ability to carry out muscular activities. In the next two items, patients are asked to circle the number of days in the past week they felt good and how often they missed work. Finally, the last seven questions (job ability, pain, fatigue, morning tiredness, stiffness, anxiety and depression) are measured by a visual analogue scale (VAS). The Spanish validated version will be used [26].

- Pain Visual Analogue Scale (PVAS): The PVAS was designed to allow a thorough and understandable subjective assessment of pain. A Visual Analogue Scale is usually a 10-cm horizontal line, with perpendicular lines on the edges, defined as the extreme limits of pain experience. Anchoring points at each edge are characterised by verbal expressions such as "No pain" (accompanied by the number "0") at one end and "maximum pain ever experienced" (accompanied by the number "100") at the other end. The adequate psychometric properties of PVAS have been demonstrated in previous studies [27,28]. The Spanish validated version of this questionnaire will be used [29].

- Pain threshold assessed by sphygmomanometer: the sphygmomanometer, a universally used clinical test, has been demonstrated to be helpful in the identification of patients with FM [30]. It has been recommended that the blood pressure cuff be inflated at an approximate rate of 10 mm Hg per second up to 180 mm Hg or to the point where pain is elicited. Healthy persons usually experience pain when the blood pressure cuff is inflated to 160 mm Hg or more; however, patients with FM usually experience pain at 100-110 mm Hg or at even lower pressure [30].

#### Secondary variables

##### Socio-demographic variables

The following socio-demographic data will be collected: sex, age, marital status (single, married/relationship, separated/divorced, and widowed), educational level (no studies, primary, lower secondary, upper secondary, and university), occupation and income. In addition, relevant clinical variables (family and personal medical and psychiatric history, length of the disorder, main symptoms and medical comorbidity) will be also assessed.

##### Pain-related psychological constructs

- Pain catastrophizing: One of the most used questionnaires for measuring this construct is the Pain Catastrophizing Scale [13]. This is a self-administered 13-item questionnaire that assesses three dimensions: rumination, magnification and helplessness. Each item is scored from 0 (not at all) to 4 (always), and total scores range from 0 to 52. It has good temporal stability, internal consistency and validity. The Spanish validated version will be used [31].

- Pain acceptance [15,16]: This variable is assessed with the Chronic Pain Acceptance Questionnaire [15]. This is 20-item self-administered inventory. There are two principle factors measured by this questionnaire: activities engagement and pain willingness. All items are rated on a 0 (never true) to 6 (always true) scale. The maximum possible total score is 120, with a higher score indicating better acceptance. The Spanish validated version will be used [32].

- Mental defeat [17]: This concept will be evaluated with the Pain Self-Perception Scale. This is a 24-item self-administered questionnaire. These statements are to be rated on a 5-point scale (0 = "Not at all/Never", 1 = "Very little", 2 = "Moderately", 3 = "Strongly", 4 = "Very strongly"), generating a total score ranging from 0 to 96. The Spanish validated version will be used [33].

- Pain psychological inflexibility [34]: the Psychology Inflexibility in Pain Scale (PIPS) has been developed to assess this core construct in ACT. It is a 16-item self-administered instrument, with two main factors labelled "avoidance" and "cognitive fusion". Participants are asked to rate how true these statements are on a 7-point Likert-type scale that ranges from ''never true'' to ''always true'', with higher scores indicating more psychological inflexibility. Its psychometric properties are considered adequate. We will validate a Spanish version of this test on an independent sample to be used in the study.

- Perceived injustice: a 12-item self-report measure, the Injustice Experience Questionnaire (IEQ) [19], was developed to measure this concept. It addresses the degree to which individuals perceive their post-disorder life as being characterized by injustice. Principal component analysis yielded a two-component solution. These factors were labelled "irreparability of loss" and "blame/unfairness". The psychometric properties of IEQ are considered adequate. We will validate a Spanish version of this test on an independent sample to be used in the study.

- Mindfulness: Several questionnaires have been used to assess the concept of mindfulness. For this study we will use one of the most widely used, the Mindful Attention Awareness Scale [21]. This is a 15-item self-administered questionnaire. Principal component analysis yielded a one-factor solution. The respondents indicate how frequently they have the experience described in each statement using a 6-point Likert scale from 1 (*almost always*) to 6 (*almost never*), where high scores reflect more mindfulness. In an attempt to monitor for socially-desirable responses, respondents are asked to answer according to what "really reflects" their experience rather than what they think their experience should be. The items are distributed across cognitive, emotional, physical, interpersonal and general domains. Psychometric properties of the questionnaire are adequate [21]. A Spanish version of this test will be validated on an independent sample to be used in the study.

-Positive and Negative Affect: This will be measured with the Positive and Negative Affect Scale (PANAS) [35]. The PANAS consists of 2 mood scales with 10 items each for the assessment of PA and NA. Scores for each scale range from 0 to 50. The scales have been shown to be internally consistent, uncorrelated and stable over a 2-month period; good convergent and discriminant validity have also been demonstrated [35]. The Spanish validated version will be used [36].

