#### Analysis strategy

At baseline, means and standard deviations will be calculated for continuous variables in the study in case of normality, or medians and interquartile periods where this hypothesis is not fulfilled. The Kolmogorov-Smirnov test will be applied to ensure the adjustment of data to a normal distribution.

The existence of differences in socio-demographic, main outcome and other variables regarding pain-related psychological constructs will be analysed. These differences will be studied using Chi Square test for qualitative variables, with the Fisher test being utilized when necessary. To determine the relationship between categorical variables with one or two levels and quantitative variables, Student T test or variance analysis will be used, respectively, for variables fulfilling the normality hypothesis. For the remaining variables, non-parametric tests such as Man-Whitney U or Kruskall-Wallis will be used. To assess the predictive value of pain-related psychological construct on main outcome variables at one-year follow-up, use will be made of a logistic regression analysis adjusted for socio-demographic and clinical variables.

A Spearman Rho non-parametric correlation matrix will be developed to determine the relationship between pain-related psychological constructs and possible overlapping, including these constructs and the other variables, for the analysis of the significance of this matrix and each one of the calculated correlations. Patients will be grouped according to pain-related psychological constructs using cluster analysis, with a profile graph to represent the results of this multivariant analysis. Data will be analysed using the SPSS 15 statistical package.

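### The acceptance score defined is a total that blends activities engagement with pain willingness, while the FIQ holds some activity and work items; report the two factors beside the total and adjust for baseline FIQ

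*Protocol article*

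**What the plan says.** All places are in the protocol article.

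- **Pain-related psychological constructs.** The acceptance questionnaire has 20 items, each rated 0 to 6. On its structure: "There are two principle factors measured by this questionnaire: activities engagement and pain willingness". On its score: "The maximum possible total score is 120, with a higher score indicating better acceptance". No score is defined for either factor. The PIPS is also described as having two factors, avoidance and cognitive fusion. No range is given for it, only that higher scores mean more inflexibility.
- **Background.** Acceptance is itself defined partly through activity: "focusing instead on participation in valued activities and the pursuit of personally relevant goals".
- **Main outcome variables.** The FIQ opens with a question on physical capacity: "The first item focuses on the patient's ability to carry out muscular activities". Two further questions cover recent good days and absence from employment. Job ability is one of the seven visual analogue questions that follow; the other six are symptoms.
- **Table 1.** The FIQ is listed as the measure of general function, taken at baseline and at follow-up.
- **Analysis strategy.** "To assess the predictive value of pain-related psychological construct on main outcome variables at one-year follow-up", logistic regression is planned, with socio-demographic and clinical covariates. Baseline FIQ is not named among them. A Spearman matrix is to show how the constructs relate and overlap. The section does not say whether totals or factor scores enter either analysis.

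**The concern.** The general aim is to judge how much the constructs matter for function and pain. The specific objective is to find correlations and overlap among the constructs. A blended acceptance total weakens both answers.

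- **Function.** One of the two acceptance factors concerns doing activities, and part of the FIQ concerns being able to do them or to work. A patient who is already active may score higher on the predictor at baseline and better on the FIQ a year later, because function tends to persist. From the total alone, a reader cannot see whether willingness to have pain or existing activity carries the association. The named covariates do not take out prior function.
- **Overlap.** Pain willingness and PIPS avoidance look, from their labels, like near opposites, but each is combined with a different second factor. A strong relation between those two factors would appear only as a moderate correlation of totals.

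**Working it through.** **1. The plan's own figure.** 20 items × 6 = 120, which agrees with the stated maximum. The defined score is the sum over all items, so it includes both factors.

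**2. How much of the FIQ concerns activity or work.** Counted from the item descriptions: 1 (muscular activities) + 2 (days felt good, missed work) + 7 (analogue scales) = 10 items. Those related to activity or work are muscular activities, missed work and job ability, so 3 of 10, the last two more loosely. The other 7 are days felt good and six symptoms. The wording of the acceptance items is not shown, so the overlap is judged from labels.

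**3. What a total can and cannot show.** Assume two equally weighted factors with unit variance and correlation f between them. Let engagement and willingness correlate c_E and c_W with the FIQ, in size. Then

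corr(total, FIQ) = (c_E + c_W) / √(2 + 2f).

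With f = 0, three different situations give the same result:

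| c_E | c_W | corr(total, FIQ) |
|---|---|---|
| 0.6 | 0 | 0.6/√2 = 0.42 |
| 0.3 | 0.3 | 0.6/√2 = 0.42 |
| 0 | 0.6 | 0.6/√2 = 0.42 |

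The total cannot tell them apart; the two factor scores can.

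**4. Why no single size can be given.** Take c_E = 0.6 and f = 0.5, both assumed.

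- If willingness is unrelated to the FIQ (c_W = 0): 0.6/√3 = 0.35. This requires a partial correlation of willingness with the FIQ, given engagement, of −(0.5 × 0.6)/√(0.75 × 0.64) = −0.43, a suppressor effect for which the article gives no basis.
- If willingness relates to the FIQ only through engagement (c_W = 0.5 × 0.6 = 0.3): 0.9/√3 = 0.52.

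The answer turns on inputs that the article does not contain.

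**5. One-year prediction, by simulation.** Assumptions: n = 305 as stated in Sample size, with no drop-out; half the variance of the total is engagement; engagement correlates 0.2 to 0.5 with baseline function; function has one-year stability of 0.5 to 0.7; acceptance has no effect of its own; the outcome is split at its median; no other covariates. The implied correlation of the total with one-year function is √0.5 × 0.2 × 0.5 = 0.07 up to √0.5 × 0.5 × 0.7 = 0.25. There were 1,000 runs per scenario:

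| Model | Significant at 0.05 | Odds ratio per SD |
|---|---|---|
| Without baseline function | 17% to 94% | 1.12 to 1.51 |
| With baseline function | 4% to 6% | about 1.0 |

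The simulation treats baseline function as measured without error, so real adjustment for the FIQ would remove most of this effect but perhaps not all.

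**6. Overlap between two scales.** If one of two uncorrelated, equally weighted factors is fully shared by two scales, the totals have covariance 1 and variance 2 each. Their correlation is 1/√(2 × 2) = 0.50 in size, or 25% shared variance, although the shared factor is identical. This is a limiting case, not an estimate for these scales.

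**The case against.** **The article describes instruments; it does not say that only totals will be analysed.** This stands. A reader might infer that the subscales will go unused, but Analysis strategy names no score level, and the choice may sit in a fuller document. For the PIPS, not even a total range is given. Against that, the same article does signal separate scores where it means them (a score range for each PANAS scale, two independent HADS subscales), and acceptance receives only a total.

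**The content overlap is thin.** It is partial: "ability to carry out muscular activities" is physical capacity, which is not the same as engaging in life despite pain, and 7 of 10 FIQ items are not about activity or work. This limits the size of the effect but does not remove it.

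**Engagement belongs to acceptance.** It does, by the definition in Background. The total is therefore a legitimate score. A reader might infer that only pain willingness is a clean measure, but using it alone would discard part of the construct that the study set out to test. It would not be immune either: where the factors correlate, willingness is linked to the FIQ through engagement (0.5 × 0.6 = 0.3 in the second case of step 4).

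**Other constructs may share content too.** A reader might infer that acceptance gains a built-in advantage over the other constructs. That is not shown. The FIQ's pain, anxiety and depression items could equally favour catastrophizing or negative affect.

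**The predictor precedes the outcome by a year.** This is right, and it means that the overlap acts mainly through persistent baseline function. That is a reason to adjust for baseline FIQ, which the stated covariates do not name.

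**Conclusion.** The point holds as a limit on interpretation; it is not a scoring error. The one acceptance score defined mixes engagement in activities with willingness to have pain, and the function outcome contains some activity and work items. An association of the total with the FIQ may therefore partly reflect existing activity level, and correlations of totals may hide overlap between single factors of the acceptance scale and the PIPS.

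The size of either effect cannot be established from the article. The simulated 17% to 94% shows that the first could be material if baseline function is left out, but it rests wholly on assumed correlations, on acceptance having no effect of its own, and on error-free measurement of function. The 0.50 rests on one factor being fully shared. Two of the three main outcomes, the pain VAS and the cuff threshold, have no activity content and are unaffected by the first effect. The stronger conclusion, that a finding for acceptance on function could never be told apart from activity level, goes too far: the data needed to examine it are being collected.

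**What to change.** 1. Keep the acceptance total, since the article's own definition includes participation in activities. In the FIQ analyses, also report activities engagement and pain willingness as separate scores. The two factors sum to the total, so fit them in a separate model from the total, not together with it.
2. In the Spearman matrix, enter the acceptance and PIPS factors beside the totals. Do not read the correlation of a factor with its own total as overlap. For the PIPS, use the factors that the planned Spanish validation supports.
3. Name baseline FIQ as a covariate in the model for one-year FIQ. The question then becomes whether acceptance predicts later function beyond present function, and the report should say so.
4. Do not restrict the conclusion about acceptance to pain willingness.

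Cost: wording only, since Table 1 already lists these questionnaires and the baseline FIQ. Splitting acceptance uses one more predictor degree of freedom, baseline FIQ uses one in its own model, and the matrix gains a few correlations.
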